### Randomisation

A software package (ALEA®) is used to support the online patient registration and randomisation, which is based on the minimization method [47]. Groups are balanced on various prognostic factors. This method has been proven to provide more balanced groups in smaller trials when compared with both restricted (stratified) and unrestricted (simple) randomisation, and is able to incorporate more prognostic factors [47–49]. The Dutch Cancer Institute provides access to the online minimization program [50].

Eligible patients are assigned in 1:1 to either GKRS or WBRT. Prognostic factors included in the minimization algorithm are:Cumulative tumour volume in the brain (≤10 cm^3^ vs. > 10 cm^3^).Histology (lung vs. other).Any systemic treatment (yes vs. no).Karnofsky Performance Status (70–80 vs. 90–100).Age (18–59 vs. 60 and over).Baseline HVLT-R (≤17 vs. 18–27 vs. ≥28, based on the trial by Chang et al., 2009).

### Statistical methods

The Bayesian power analysis and interim analyses are based on the randomised trial by Chang and colleagues [45]. An independent statistician will do interim monitoring of this trial using Bayesian statistical methods [51, 52]. Each patient’s HVLT-R total recall score recorded at 3 months is assigned a binary outcome: A decline in the total recall score of 5 points or greater compared with baseline will be considered a *failure* (0). A stable or improved score, or a decline of 4 points or less compared with baseline will be considered a *success* (1). The failure rate for treatment *k* is designated *qk*. The prior failure rates for both treatment groups will be modelled as Beta(2.09, 2.91)-distributions, with a mean of 0.42 for both groups (for details see Appendix). During the trial, stopping rules specify that in the case of a probability greater than 0.975 for the event that the failure rate of one treatment group is higher than the failure rate of the other treatment group, we will stop randomising patients to that treatment-arm. In this case, the study is terminated prematurely and the central research question will be answered. If the effect sizes are comparable to earlier accounts in the literature (following Chang et al. an effect size of 0.30 is expected), the early stopping rule will likely come into effect when 46 patients are enrolled (23 patients at 3-months follow-up in both groups; for details see Appendix).

Group analyses are carried out on an intent-to-treat principle. Raw cognitive test scores are compared with published normative values according to age (and, if available, to education) and converted into standardized scores. Cognitive impairment is defined as test performance at or below − 1.5 SD from the normative mean [6, 53]. Reliable change indices (RCI), reflecting change at the individual level in the context of observed changes based on published normative data, correcting for measurement errors are calculated, since group results may mask the variability in individual responses to the intervention [44]. Number of patients, who have improved versus the number of patients who remained stable, or declined, will be counted for all follow-up assessments. These will be compared over conditions with chi-square tests.

Repeated measures analysis of variance with adjustment for potential confounders will be used, comparing subsequent follow-ups to baseline to assess cognitive change of group means over time and across treatment arms. These analyses are similar to those of the study of Chang et al. in which an identical cognitive endpoint was formulated [45].

Missing data, if not too many, will be explicitly or implicitly (dependent on the statistical technique of choice) imputed to facilitate intention-to-treat analysis. Multiple imputation may be used for explicit imputation of missing values. Alternatively, we may use linear mixed models that implicitly deal with missing data under the assumption of missing at random.

Type and duration of systemic therapy and medication use will be taken into account if necessary.

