**Discussion:**

Knowledge gained from this trial may be used to inform individual patients with BM more precisely about the cognitive effects they can expect from treatment, and to assist both doctors and patients in making (shared) individual treatment decisions. This trial is currently recruiting. Target accrual: 23 patients at 3-months follow-up in both groups.

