## Methods/design

### Trial design

CAR-Study B is a two-arm randomised trial. Adult cancer patients (*n* = 46), with 11–20 BM, Karnofsky Performance Status (KPS) ≥ 70 and a life expectancy of at least 3 months, are screened for inclusion and exclusion criteria (Table 1) by the radiation-oncologist. Eligible patients are invited for study participation at their first visit at the Gamma Knife Centre. During this first consultation, patients receive an information letter about the study and its procedures.

**Table 1 Tab1:** Eligibility criteria - inclusions and exclusions

Inclusion criteria	Exclusion criteria
• Histologically proven malignant cancer	• Primary brain tumour
• Gadolinium-enhanced volumetric MRI-scan showing 11–20 newly diagnosed BM	• A second active primary tumour
	• Small Cell Lung Cancer, Lymphoma, Leukaemia, Meningeal disease
• Cumulative tumour volume in the brain ≤30 cm^3^	• Prior brain treatment (radiation/surgery)
• Lesion > 3 mm from the optic apparatus	• Upfront planned surgery after GKRS
• Patient age ≥ 18 years	• History of a significant neurological or psychiatric disorder
• Karnofsky Performance Status ≥70	• Participation in a concurrent study in which neuropsychological or quality of life assessments are involved
• Anticipated survival ≥3 months	• Underlying medical condition precluding adequate follow-up
• Patient informed consent obtained (verifying that patients are aware of the investigational nature of this study)	• Patients unable to complete test battery due to any of the following reasons:
• Patients can be undergoing concurrent systemic therapy at the discretion of their treating oncologist	○ Lack of basic proficiency in Dutch
	○ IQ < 85
	○ Severe aphasia
	○ Paralysis grade 0–3 (MRC scale)
	○ Severe visual problems

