After signing a written informed consent statement, co-signed by the principle investigator or a formally delegated authorized person, a baseline neuropsychological assessment (NPA) is performed. Subsequently, patients are randomised by the method of minimisation 1:1 to either GKRS (*n* = 23) or WBRT (n = 23). The trial schema and randomisation factors are shown in Fig. 1. The trial has been approved by the local medical ethics review committee (METC Brabant, The Netherlands). Patients from both arms are followed up at 3, 6, 9, 12 and 15 months after treatment. High rates of attrition and noncompliance are very common in trials in patients with metastatic disease [14, 41]. In an attempt to maximize patient comfort and convenience, the administration of the test battery and additional questionnaires is combined with usual care clinical visits on site (3-monthly contrast MRI-scans and consult with the radiation-oncologist).

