### Participants

Patients who meet the inclusion and exclusion criteria (Table 1) are eligible for the study. It is projected to include 46 patients.

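### The figure of 46 patients (23 per arm) serves both as the number randomised and as the number assessed at 3 months, with no allowance for loss in between

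*Protocol article*

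**What the plan says.** The protocol article gives the size of the trial in several places, and they do not describe the same set of patients.

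- **As the number included or randomised.** Trial design gives n = 46 for the trial and 23 for each arm at randomisation: "patients are randomised by the method of minimisation 1:1 to either GKRS (*n* = 23) or WBRT (n = 23"). Participants adds: "It is projected to include 46 patients".
- **As the number followed to 3 months.** The Discussion paragraph of the abstract says: "Target accrual: 23 patients at 3-months follow-up in both groups".
- **As both at once.** Statistical methods says that "the early stopping rule will likely come into effect when 46 patients are enrolled (23 patients at 3-months follow-up in both groups").

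The Appendix takes 23 patients in each group and a difference of 0.30 and reports an expected probability of 0.975 that the WBRT failure rate is the larger. The monitoring rule works on the HVLT-R total recall score recorded at 3 months, classed as failure or success.

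On losses, Trial design states: "High rates of attrition and noncompliance are very common in trials in patients with metastatic disease". The survival criterion in Table 1 is "Anticipated survival ≥3 months". The article gives no attrition rate and no inflation of the sample size.

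**The concern.** The number randomised equals the number with a 3-month score only if every randomised patient survives to 3 months and completes the HVLT-R. The protocol gives reason to doubt this: it describes attrition as very common in metastatic disease, and the primary endpoint falls at the minimum survival anticipated for entry.

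At stake is the probability that supports the sample size. If recruitment closes at 46 randomised, the Appendix figure describes a larger evaluable sample than the trial can be expected to have. If recruitment instead runs until 23 per arm have been assessed, the number to be randomised is understated in Trial design, Participants and Statistical methods. Either way, a reader cannot tell when accrual ends.

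**Working it through.** **Inputs from the protocol.** Prior: "The prior failure rates for both treatment groups will be modelled as Beta(2.09, 2.91)-distributions, with a mean of 0.42 for both groups" (Statistical methods). Difference: "an effect size of 0.30 is expected" (Statistical methods and Appendix). Sample: 23 per arm. Threshold: 0.975.

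**Inputs assumed.** The arm-specific failure rates are not stated. Centring a difference of 0.30 on the prior mean of 0.42 gives 0.57 (WBRT) and 0.27 (GKRS). Pairs from 0.50/0.20 to 0.65/0.35 were also tried. The attrition rate is not stated, so 10%, 20%, 30% and 40% loss by 3 months are shown as a range.

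**Step 1: reproduce the protocol's figure.** With n per arm and the observed failures set at their expected values n·p, each arm's posterior is Beta(2.09 + n·p, 2.91 + n·(1 − p)). At n = 23:

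- WBRT: 2.09 + 23 × 0.57 = 15.2 and 2.91 + 23 × 0.43 = 12.8, so Beta(15.2, 12.8).
- GKRS: 2.09 + 23 × 0.27 = 8.3 and 2.91 + 23 × 0.73 = 19.7, so Beta(8.3, 19.7).
- P(q_WBRT > q_GKRS), by numerical integration, is 0.972.

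Across the other pairs the result runs from 0.970 (0.65/0.35) to 0.976 (0.50/0.20). This agrees with the Appendix's 0.975 and needs no dropout term. The 23 per arm behind that figure are therefore patients with an outcome.

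**Step 2: 46 randomised, some lost.** The evaluable number per arm is 23 × (1 − d).

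| Assumed loss d | 23 × (1 − d) | Evaluable per arm, rounded | Posterior at 0.57/0.27 | Range over rate pairs |
|---|---|---|---|---|
| 0% | 23.0 | 23 | 0.972 | 0.970–0.976 |
| 10% | 20.7 | 21 | 0.965 | 0.963–0.969 |
| 20% | 18.4 | 18 | 0.951 | 0.949–0.956 |
| 30% | 16.1 | 16 | 0.939 | 0.936–0.944 |
| 40% | 13.8 | 14 | 0.923 | 0.920–0.928 |

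**Step 3: number to randomise for 23 evaluable per arm.** This is 23 / (1 − d), rounded up within each arm because allocation is 1:1.

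| Assumed loss d | 23 / (1 − d) | Per arm | Total |
|---|---|---|---|
| 10% | 25.6 | 26 | 52 |
| 20% | 28.75 | 29 | 58 |
| 30% | 32.9 | 33 | 66 |
| 40% | 38.3 | 39 | 78 |

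**The case against.** The strongest reply is that the abstract already defines the target by patients at 3 months, and that the parenthesis in Statistical methods repeats it. On that reading, accrual continues until 23 per arm have been assessed, the Appendix figure is untouched, and only the words for enrolment and inclusion are loose. Participants speaks of a projection, and Statistical methods predicts when stopping is likely without setting a cap. This reading is tenable, and it limits the point. A reader might infer that the authors knowingly assumed zero attrition, or that the trial will end short of evaluable patients. The documents do not establish either. But Trial design randomises 23 to each arm, so the statements still conflict.

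A second reply is that the authors did consider losses. Testing is combined with usual-care visits, the 3-month time point was chosen to keep as many enrolled patients as possible assessable, and missing data may be imputed. These measures may reduce loss, but none changes the stated number. Imputation is foreseen only if there are not too many missing values. The monitoring rule uses recorded scores, and imputing outcomes does not restore the lost information.

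A third reply is that the fall in the posterior depends on assumed rates and is small at 10% loss (0.972 to 0.965). That is correct. At 0.57/0.27 the posterior is also slightly under 0.975 with no loss at all, so that part of the gap must not be put down to attrition.

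**Conclusion.** The inconsistency stands. The protocol uses 46 for two populations that coincide only if no one is lost before 3 months, and its supporting probability belongs to the evaluable one. This is a conflict in how the sample size is defined. The arithmetic is not at fault, since 23 + 23 = 46 and the 0.975 reproduces.

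The size of the consequence is conditional. If recruitment stops at 46 randomised, the failure rates are 0.57 and 0.27, and loss is 10% to 40%, the posterior at the expected data is 0.965 to 0.923 instead of 0.972. The loss rate and the arm rates are assumptions, and the document does not make any one scenario the expected one. If accrual runs to 23 evaluable per arm, the probability holds and the stated number randomised is too low.

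A reader might go further and take the 0.975 as the chance that the rule will be met, then blame attrition for a low chance. The figure is a posterior probability at the expected data. The chance of crossing the threshold is limited even with complete follow-up, which is a separate matter and no part of this conclusion.

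**What to change.** State one target and use it throughout. There are two ways:

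1. Define 46 everywhere as patients with a 3-month HVLT-R score, 23 per arm. State an attrition assumption and give the number to randomise that follows from it: 52, 58, 66 or 78 for 10%, 20%, 30% or 40% loss.
2. Keep 46 randomised, state the attrition assumption, and restate the Appendix probability for the evaluable number that it implies.

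Under either option, reword the sentence in Statistical methods so that the rule is expected to take effect once 46 patients have a 3-month HVLT-R score, instead of once 46 are enrolled. The latest patients enrolled will not yet have the outcome that the rule uses.

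The cost is wording in the abstract, Trial design, Participants, Statistical methods and the Appendix, plus one short calculation. The first option also commits the trial to recruiting more patients than the 46 now projected. The second gives a less favourable probability than the one now printed.

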The more persistent *late delayed* effects of radiation on cognitive functioning become apparent 6–12 months after treatment [22] and may be most disruptive for patients’ quality of life. For this reason, we have also included long-term assessments in our design. Information on test performance in long-term survivors is essential for complete comprehension of the course of cognitive functions over time, even though many of the enrolled patients may have deceased at this point in the study.

This study may be highly relevant in clinical decision-making; knowledge gained from this trial may possibly change clinical practice and international guidelines on BM. For example, thus far in the Netherlands, the standard of care for patients with multiple brain metastases (> 4) has remained WBRT. Ultimately, the purpose of CAR-Study B is to inform patients and doctors which treatment modality, GKRS or WBRT, best preserves cognitive functions and quality of life. This will enable patients and doctors to make shared treatment decisions grounded on scientific evidence and consequently maximize the clinical outcome of each individual patient.

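### For change in mean scores, the plan commits only to repeated-measures ANOVA and leaves methods that keep partial records optional, although it expects high attrition and deaths

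*Protocol article*

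**What the plan says.** The protocol article, under Trial design, sets five assessments after baseline: "Patients from both arms are followed up at 3, 6, 9, 12 and 15 months after treatment". For change in group means over time and between arms, Statistical methods states: "Repeated measures analysis of variance with adjustment for potential confounders will be used, comparing subsequent follow-ups to baseline". This is the only method for that purpose that the section states as a commitment.

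The next paragraph deals with incomplete data: "Missing data, if not too many, will be explicitly or implicitly (dependent on the statistical technique of choice) imputed to facilitate intention-to-treat analysis". It goes on: "Multiple imputation may be used for explicit imputation of missing values". Then: "Alternatively, we may use linear mixed models that implicitly deal with missing data under the assumption of missing at random". The section also sets a general principle: "Group analyses are carried out on an intent-to-treat principle".

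The article is open about what to expect. Trial design says: "High rates of attrition and noncompliance are very common in trials in patients with metastatic disease". The Discussion defends keeping the long-term assessments, "even though many of the enrolled patients may have deceased at this point in the study". Neither place gives a rate.

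**The concern.** The firm commitment and the expected data do not fit together. A classical repeated-measures ANOVA across several visits needs a complete set of scores from each patient. The methods that avoid this requirement appear only as possibilities. The imputation provision has a condition with no threshold, and the article's own expectations suggest that the condition may well fail. If it does, no other method is fixed, and an ANOVA on complete records is the natural default.

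Two things would then be at stake. Early scores from patients who later died or stopped attending would be discarded. The arms would also be compared among patients selected by what happened after randomisation, which does not sit well with the stated intention-to-treat principle. In addition, three approaches with different samples and assumptions stay open, and the choice between them could be made after the data are seen.

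**Working it through.** **Inputs.** From the article: 46 patients, 23 per arm, and five follow-ups at three-month intervals. Assumed, because the article gives no attrition rate: a constant loss *a* per interval of 10, 20 or 30%, permanent once it occurs. The article has no figure of its own to reproduce for the longitudinal analysis. Its 0.975 probability at 46 patients concerns the three-month primary endpoint and is not used here.

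**Reading 1: one ANOVA over all six assessments, no imputation.** Patients with every visit = 46 × (1 − a)^5. Patients with a three-month score = 46 × (1 − a).

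| Assumed loss per interval | With every visit | With three-month data | Three-month scores discarded |
|---|---|---|---|
| 10% | 46 × 0.590 = 27.2 | 46 × 0.9 = 41.4 | 14.2 |
| 20% | 46 × 0.328 = 15.1 | 46 × 0.8 = 36.8 | 21.7 |
| 30% | 46 × 0.168 = 7.7 | 46 × 0.7 = 32.2 | 24.5 |

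The abstract can be read as counting the 46 at three months rather than at randomisation. On that count the complete records are 46 × (1 − a)^4 = 30.2, 18.8 and 11.0, against 46 with three-month data.

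**Reading 2: baseline against each follow-up separately, no imputation.** Patients at visit *k* = 46 × (1 − a)^k.

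| Assumed loss | 3 mo | 6 mo | 9 mo | 12 mo | 15 mo |
|---|---|---|---|---|---|
| 10% | 41.4 | 37.3 | 33.5 | 30.2 | 27.2 |
| 20% | 36.8 | 29.4 | 23.6 | 18.8 | 15.1 |
| 30% | 32.2 | 22.5 | 15.8 | 11.0 | 7.7 |

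No three-month score is lost to a later absence. The late comparisons still rest on those alive and tested, and at 15 months the counts equal those of Reading 1.

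**Check with a different attrition model (Reading 1).** Let survival be exponential with assumed median *m* months, and let survivors miss each visit with assumed probability *c*. Patients with every visit = 46 × 0.5^(15/m) × (1 − c)^5.

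| Assumed median survival | c = 0 | c = 10% | c = 20% |
|---|---|---|---|
| 6 months | 8.1 | 4.8 | 2.7 |
| 9 months | 14.5 | 8.6 | 4.7 |
| 12 months | 19.3 | 11.4 | 6.3 |
| 18 months | 25.8 | 15.2 | 8.5 |

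For medians of 6 to 12 months this gives about 3 to 19 of 46. At c = 10%, a method that also uses partial records would have about 29 patients at three months and 21 at six months (median 6 months), or 35 and 29 (median 12 months). The counts from constant loss are therefore not extreme.

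**The case against.** The strongest reply is that the article already deals with missing data. The paragraph after the ANOVA sentence provides for imputation, names multiple imputation and linear mixed models, and serves an intention-to-treat analysis. A reader might infer that the plan is a complete-case analysis. The text does not support that: under either remedy the analysis is not confined to complete records. What remains is that both remedies are optional and that imputation depends on an undefined amount of missing data.

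A second reply is that comparing follow-ups with baseline may mean separate pairwise analyses. This is a fair reading. It removes the loss of early scores shown under Reading 1, and with two time points the usual covariance assumption is met automatically. It does not remove the dependence of late results on survivors.

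Third, the choice of model is often left to the analysis plan, which is not shown. That would answer a complaint about missing detail. Here, however, the article does state a method, and it is one poorly matched to the data it expects.

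Other stronger claims should not be made. The article does not rank its secondary endpoints, so this is not its main secondary result; some secondary results are visit-by-visit percentages that do not use ANOVA. It does not say that scores would be imputed after death, although it does not exclude this. Nor does naming the ANOVA amount to assuming equal correlation between visits: the univariate form needs sphericity, which is weaker, and standard corrections exist.

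**Conclusion.** The point holds in a limited form. Repeated-measures ANOVA is the committed method for change in group means. The methods that keep partial records are optional, and imputation is conditional on few missing data where the article anticipates many. The counts of 27, 15 and 8 complete records, against 41, 37 and 32 patients with three-month data, hold only for a single six-assessment ANOVA without imputation, at an assumed loss of 10, 20 and 30% per interval. They are illustrations, not forecasts. With separate baseline-to-visit comparisons the loss is smaller, and the remaining problem is survivor selection at the late visits. The matter concerns secondary analyses only; the three-month primary endpoint and the sample size of 46 are unaffected. The plan should be changed here because a better method is already on its own list.

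**What to change.** Replace the repeated-measures ANOVA with a linear mixed model as the main longitudinal analysis. Include arm, visit as a category, arm-by-visit interaction, baseline score and the minimisation factors, and use all available scores from all randomised patients. Drop the condition on the amount of missing data for this analysis.

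Report the number alive and the number tested, by arm, at each visit. State that the 9- to 15-month contrasts assume data missing at random and implicitly extrapolate scores past death. They should therefore not be labelled as conditional on survival. Show the observed means among survivors alongside, as description only.

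The cost is a small change in analysis wording, with no extra data. The downside is reliance on the missing-at-random assumption, which the plan already names and which does not settle what a score after death should mean. That is why the extrapolation has to be stated openly.

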#### Neuropsychological assessment (NPA) and patient-reported outcomes (PROs)

A reliable, valid neuropsychological test battery (Table 2) is used to assess cognitive functioning [40, 42, 43] and is administered by a trained neuropsychologist. In addition, measures of patient-reported outcomes (PROs) are used to assess anxiety and depression, quality of life and fatigue (Table 2). The total time for neuropsychological test administration, including assessment of PROs, ranges from approximately 60 to 90 min.

**Table 2 Tab2:** Neuropsychological test battery and patient-reported outcomes (PROs)

Cognitive Domain	Cognitive Test
Verbal memory	Hopkins Verbal Learning Test-Revised (HVLT-R)
Cognitive flexibility	Trail Making Test B (TMT B)
Word Fluency	Controlled Oral Word Association (COWA)
Working memory	Wechsler Adult Intelligence Scale - Digit Span
Processing speed	Wechsler Adult Intelligence Scale - Digit Symbol
Motor dexterity	Grooved Pegboard (GP)
Patient Reported Outcomes	Questionnaire
Quality of life	Functional Assessment of Cancer Therapy-Brain (FACT-Br)^a^
	• Physical well-being (PWB)
	• Functional well-being (FWB)
	• Social well-being (SWB)
	• Emotional well-being (EWB)
	• Brain Cancer Subscale (BRCS)
Fatigue	Multidimensional Fatigue Inventory (MFI)^a^
	• General fatigue
	• Reduced motivation
	• Physical fatigue
	• Mental fatigue
	• Reduced activity
Anxiety and depression	Hospital Anxiety and Depression Scale (HADS)^b^
	• Anxiety
	• Depression

^a^Published normative data of FACT-Br and MFI are used for the interpretation of quality of life and fatigue scores [55, 56]

^b^A cut-off point ≥8 is used to indicate symptoms of depression or anxiety [57]

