#### Secondary endpoints

Differences in percentages of patients with a ≥ 5-point decrease in HVLT-R total recall between treatment arms are evaluated at 6, 9, 12 and 15 months as is done for the primary endpoint at 3 months.Group mean scores for all neuropsychological tests and questionnaires are determined for both treatment arms at baseline, 3, 6, 9, 12 and 15 months.Percentages of patients with cognitive impairment are determined at baseline, 3, 6, 9, 12 and 15 months.Overall survival is calculated as the time from the first day of treatment to date of death.The RANO-BM criteria (Response Assessment in Neuro-Oncology Brain Metastases [46]) are used to determine local and distant tumour control.

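### The secondary group-mean analysis of cognition compares the arms on change from baseline, which is less precise than adjusting for each test's own baseline score

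*Protocol article*

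**What the plan says.** The Statistical methods section of the protocol article names both the model and the contrast for mean scores. The model: "Repeated measures analysis of variance with adjustment for potential confounders will be used". The contrast: "comparing subsequent follow-ups to baseline to assess cognitive change of group means over time and across treatment arms". The confounders are not named.

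The Secondary endpoints section puts baseline in the same list as the five follow-up visits: "Group mean scores for all neuropsychological tests and questionnaires are determined for both treatment arms at baseline, 3, 6, 9, 12 and 15 months".

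A second model appears in the paragraph on missing data: "Alternatively, we may use linear mixed models that implicitly deal with missing data under the assumption of missing at random". It is optional, and the article does not say how baseline would enter it.

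The Randomisation section introduces its list with "Prognostic factors included in the minimization algorithm are". The only test score on that list is baseline HVLT-R, in three bands. The other five tests in Table 2 (TMT B, COWA, Digit Span, Digit Symbol, Grooved Pegboard) are not on it.

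**The concern.** If baseline is one of the repeated outcomes, the arm effect is the arm-by-time contrast, that is, the difference between arms in change from baseline. This fixes the coefficient of the baseline score at 1. In a randomised trial the best coefficient is the regression slope of follow-up on baseline, which equals r when the variances are equal and so lies below 1 whenever the correlation is imperfect. Fixing it at 1 adds noise.

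What is at stake is precision in cognitive functioning over time, the first secondary outcome listed. The design aims for "23 patients at 3-months follow-up in both groups", and the article expects fewer patients at later visits through attrition and death.

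**Working it through.** **Inputs.** The article gives 23 patients per arm and 1:1 allocation. It gives no expected effect, standard deviation or correlation for any mean score, so there is no planned figure to reproduce; the 0.30 effect and the 0.975 probability belong to the binary primary endpoint. Assumed here: equal variance at baseline and follow-up (SD = 1), one follow-up visit, complete data, and r between 0.5 and 0.9.

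**Step 1, variance per patient.**
- Change score: 1 + 1 - 2r = 2(1-r).
- Follow-up adjusted for baseline: 1 - r².
- Ratio: (1-r²) / [2(1-r)] = (1+r)/2, below 1 for every r below 1.

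**Step 2, standard error of the arm difference.** With n = 23 per arm, SE = √(variance × 2/23), in SD units.

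| r (assumed) | Change variance | Adjusted variance | Ratio | SE, change | SE, adjusted |
|---|---|---|---|---|---|
| 0.5 | 1.00 | 0.75 | 0.75 | 0.295 | 0.255 |
| 0.6 | 0.80 | 0.64 | 0.80 | 0.264 | 0.236 |
| 0.7 | 0.60 | 0.51 | 0.85 | 0.228 | 0.211 |
| 0.9 | 0.20 | 0.19 | 0.95 | 0.132 | 0.129 |

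The formula treats the slope as known. A simulation of 20,000 trials that estimates it gives adjusted SEs of 0.258, 0.237 and 0.213 at r = 0.5, 0.6 and 0.7, against 0.294, 0.262 and 0.228 for change. Estimating the slope therefore uses up little of the gain.

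**Step 3, the same in patients and power.** To match the change score at 23 per arm, adjustment needs 23 × (1+r)/2 patients: 17.2 per arm at r = 0.5 and about 19.5 at r = 0.7. For an illustrative difference of 0.6 SD (an assumption; two-sided 5%), power goes from 53% to 65% at r = 0.5 and from 75% to 81% at r = 0.7.

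**Step 4, chance baseline imbalance.** If the arms differ at baseline by D and there is no treatment effect, the expected follow-up difference is rD. The change contrast subtracts all of D, so its expected value is rD - D = -(1-r)D. With D = +0.5 SD this is -0.25 SD at r = 0.5 and -0.15 SD at r = 0.7. Simulated means are -0.249 and -0.148, against -0.002 and 0.002 with baseline adjustment. Under simple randomisation at 23 per arm, D has SE √(2/23) = 0.295 SD and exceeds 0.5 SD in either direction with probability 9% per test.

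**Step 5, steps 2 and 4 are one loss.** Algebraically, 2(1-r) - (1-r²) = (1-r)². At r = 0.6 the extra variance of the change contrast is (0.80 - 0.64) × 2/23 = 0.0139. The variance contributed by the imbalance is (1-r)² × 2/23 = 0.16 × 2/23 = 0.0139. They are the same quantity.

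**The case against.** **The text is short and leaves room.** This is a condensed article. The confounders are unnamed, and a mixed model with equal baseline means would fit within the option given. Covariate lists are often left to an analysis plan. This stands to the extent that the change-score reading is a reading, though the natural one. But the article does state a contrast, and a baseline that is already an outcome level is not also a covariate. The mixed model is offered only for missing data.

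**The trial's aim is change in cognitive performance.** An arm-by-time contrast estimates that directly. So does the adjusted comparison: randomisation makes the baseline means equal in expectation, so both contrasts target the same arm difference.

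**Stronger readings that the article does not support.**
- A reader might infer that chance baseline differences go uncorrected in the five tests outside the minimisation. They do not: a change score removes the whole difference, which is too much. Nor is the limit to five tests exact, because HVLT-R is balanced only within three bands and minimisation does not replace adjustment in the model.
- A reader might count imbalance as a second harm, or as systematic bias. Step 5 shows that it is the precision loss again, and it averages to zero over randomisations.
- A reader might call the loss large relative to plausible effects. The article gives no expected effect for any mean score, so this cannot be judged.
- A reader might extend the point to the questionnaires. The model sentence speaks of cognitive change, so its application to FACT-Br, MFI and HADS is less certain.

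**The 0.295 SD figure assumes simple randomisation.** Minimisation on age, KPS, histology, tumour volume and systemic treatment, together with standardisation of scores by age, may reduce imbalance in tests related to those factors. This is fair, and it is a reason to treat the 9% as illustrative.

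**Conclusion.** The point holds as one of efficiency. On the natural reading, the planned group-mean comparison is a valid change-from-baseline contrast that discards precision the trial could have from data it already collects. Baseline adjustment gives 75% to 85% of the change-score variance for an assumed r of 0.5 to 0.7. The gain shrinks to 5% at r = 0.9, where it hardly matters. In a particular trial with a chance baseline difference, the change contrast is off by (1-r) times that difference in the opposite direction; this is conditional error, not bias of the method.

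The size rests on assumed correlations, equal variances, a single visit and complete data at 23 per arm. The direction holds for any r below 1 under that model, apart from the small cost of estimating the slope. The effect is confined to the secondary analysis of mean cognitive scores. The binary HVLT-R endpoint at 3 months and the Bayesian stopping rule do not use this model.

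**What to change.** In Statistical methods, replace the sentence on repeated measures analysis of variance with wording such as: For each cognitive test, the scores at 3, 6, 9, 12 and 15 months are the outcomes; the baseline score of the same test is a covariate; the arm difference is estimated at each visit. Changes from baseline within each arm are reported descriptively.

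An alternative is the linear mixed model that the article already allows, with baseline kept among the outcomes and the two arms' baseline means constrained equal. If the same approach is meant for the questionnaires, say so.

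The cost is wording plus about one degree of freedom per model; the baseline values are already collected. Adding the six minimisation factors as covariates should remain optional: with at most 46 patients, and fewer at late visits, those extra parameters are not free.
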